#### Informed consent

After patients have had sufficient time to reflect and decide to give written informed consent, they will be registered as participants in the trial.

#### First preoperative assessment

Participating patients will be asked to arrive at the waiting room of both outpatient Oral and Maxillofacial surgery clinics, 1 hour and 15 minutes prior to their appointment for ingestion of study medication, for a diagnostic interview and filling out questionnaires. Demographic variables (age, sex, highest level of education marital status, and country of birth) will be recorded.

Next, the presence of specific (that is, dental phobia in accordance with the DMS-IV TR criteria updated in 2000 [53] will be assessed using *the Phobia Checklist* containing four questions based on the DSM-IV TR criteria, developed for the assessment of dental phobia [54]. The Phobia Checklist contains four questions based on the Diagnostic and Statistical Manual of Mental disorders, text revision (DSM-IV TR) [53] criteria for specific phobia, developed for the assessment of dental phobia [54]. The Phobia Checklist has been validated and proven to be a valid diagnostic tool for this purpose (sensitivity = 0.95, specificity = 0.99, and an overall hit rate of 97 %). The presence of specific (that is, dental) phobia in accordance with the DSM 5 criteria updated in 2013 [55] will be indexed using an adapted version of *The Mini International Neuropsychiatric Interview Plus, Dutch version 5.0.0 section “Specific phobia” (H). The MINI-Plus* [56] is a structured diagnostic interview to systematically assess DSM-IV and 10^th^ revision of the International Classification of Diseases and Related Health Problems (ICD-10) diagnoses. A recent version of the MINI-Plus is not available; therefore, an adapted version will be used in which the new DSM 5 criteria [55] are addressed. Since only the presence of a specific phobia is of interest, only the section “Specific phobia” (H) will be used to assess the dichotomous specific phobia outcome.

To identify the memories of distressing events that initiated or exacerbated dental anxiety, the *Full Intrusions Interview,* a modified semi-structured interview adapted from Reynold and Brewin (1999) [57] will be used. Patients will be asked to report any spontaneous autobiographical memory that kept coming to mind over the previous week from a past event. If the last week had been exceptional, they will be prompted to think back to a typical week, or a week shortly before a dental appointment. The participant will be requested to identify the most disturbing memory. Based on this memory, the investigator will compose and record an approximately 30-second personal memory script, portraying the experience. This script of the most crucial traumatic memory is called M1. Characteristics of this memory will be subsequently determined (that is, avoidance and aversiveness propensity, the sense of here and now, the impact of and burden caused by the memory), after which patients will be requested to rate these characteristics on standardized continuous self-report VASs ranging from 0 to 100.

#### Treatment allocation

After the interview, patients will be randomized and allocated to receive either perioperative oral propranolol capsules or placebo capsules. Both groups will undergo two regular dental extraction procedures, with a 4-week interval.

#### First dental extraction procedure

One hour and 15 minutes before the surgery, participants will be approached by the investigator. They will then receive the first two capsules of study medication. The intervention group will receive 80 mg of oral propranolol (2 capsules) 1 hour and 15 minutes prior to treatment, and 40 mg of oral propranolol (1 capsule) directly after treatment. The control group will receive oral placebo capsules in the same order. The following hour is reserved to allow time for achieving an optimal plasma concentration of propranolol.

In the period between ingestion of the study medication and the surgery, a 30-minute screening by an investigator will take place (see paragraph: “Study outcome measures”). All outcomes will be registered on a case report form (CRF). After the interview, the patients will be guided back to the waiting room by the investigator. Next, they will be invited into the operating room by their surgeon. The surgeon will be either a senior staff member or a resident in Oral and Maxillofacial Surgery. During this first procedure, a prilocaine 3 % with felypressin (1:850,000) solution will be administered as local intraoral anesthetic to prevent a possible unwanted α-pressor reaction; a rare and potentially harmful pharmacological interaction of ß-adrenoreceptor antagonists with adrenaline that may result from the intravascular injection of the local anesthetic, causing bradycardia and hypertension.

In case of patients with a high level of fear of dental extractions, the surgeon will be notified that the patient has a “high or extreme” fear of dental extractions (the level of fear is not specified further) and is instructed to treat the patients accordingly.

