### Primary aim

The primary aim of this study is to determine whether administration of the active substance (two 40 mg propranolol capsules 1 hour prior to dental extraction, followed by one 40 mg capsule immediately postoperatively) results in a significantly greater reduction of dental trait anxiety in patients with self-reported high to extreme fear in anticipation of dental extraction, compared to the effects of the placebo comparator, from baseline to 4-week follow-up appointment.

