### Study outcome measures

Dependent variables were derived from the questionnaires listed below (see Tables 1 and 2).

**Table 1 Tab1:** Primary and secondary study outcome measures

		Measures			
		Primary outcome	Secondary outcomes		
		Trait anxiety (S-DAI)	State anxiety (VAS score)	Vividness/emotional charge (M1) propensity (VAS scores)	Physiological response (HR/BP)
Screening (t = 0)	Screening interview				
Intervention (t = 1)	Preoperative interview	X		X	X
	Postoperative interview		X		
Follow-up (t = 2)	Preoperative interview	X		X	X
	Postoperative interview		X		

*Note:*
*BP* blood pressure, *HR* heart rate, *M1* crucial fear-related memory, *S-DAI* Short version of the Dental Anxiety Inventory, *VAS* visual analog scale

**Table 2 Tab2:** Tertiary outcome measures

		Measures							
		Operative variables/qualitative aspect of the surgical experience (VASs)	Test of blind	IES	FCDS	Qualitative aspect of memory M2 (VASs)	Qualitative aspect of memory M1 (VASs)	Intrusions diary	Specific phobia diagnosis
Screening (t = 0)	Screening interview				X				X
Intervention (t = 1)	Preoperative interview			X			X		
	Postoperative interview	X	X			X		X	
Follow-up (t = 2)	Preoperative interview			X	X	X	X		X
	Postoperative interview	X						X	

*Notes:*
*FCDS* fear of stimuli compromising the dental setting, *IES* Impact of Event Scale - Revised, *M1* crucial fear-related memory, *M2* memory of recent dental extraction procedure, *VAS* visual analog scale

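### The protocol contradicts itself on whether the baseline S-DAI, M1 ratings and heart rate/blood pressure are taken before or after the first capsules

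*Protocol article*

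**What the plan says.** Four places in the protocol article bear on the order of events at the first visit.

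- **First preoperative assessment.** Patients arrive "1 hour and 15 minutes prior to their appointment for ingestion of study medication" for an interview and questionnaires. The phobia diagnosis is made here, M1 is elicited, and several features of M1 are rated on visual analog scales. S-DAI, heart rate and blood pressure are not named, and the listed M1 features do not include vividness or emotional charge.
- **Treatment allocation.** "After the interview, patients will be randomized and allocated to receive either perioperative oral propranolol capsules or placebo capsules".
- **First dental extraction procedure.** The investigator meets the patient 1 hour 15 minutes before surgery. "They will then receive the first two capsules of study medication". Then: "In the period between ingestion of the study medication and the surgery, a 30-minute screening by an investigator will take place", with a pointer to the section on outcome measures. The time is explained as follows: "The following hour is reserved to allow time for achieving an optimal plasma concentration of propranolol".
- **Study outcome measures.** Table 1, titled "Primary and secondary study outcome measures", leaves the t = 0 row empty. S-DAI, M1 vividness/emotional charge and heart rate/blood pressure first appear at the t = 1 preoperative interview. Table 2 lists the phobia diagnosis at t = 0 and the other M1 ratings at the t = 1 preoperative interview.

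The primary outcome and these secondary outcomes are defined as changes from baseline to 1 month. The second extraction is done without study medication. The Statistical analysis plan section allows the baseline score as a covariate if the arms differ at baseline.

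**The concern.** A change from baseline measures a treatment effect cleanly only if the baseline precedes treatment. If the t = 1 preoperative measures follow the 80 mg dose, the propranolol arm's starting value already contains part of the drug's effect, while the follow-up value is drug-free.

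This matters most for heart rate and blood pressure, on which a beta-blocker acts directly. A lowered start followed by a return to the drug-free level looks like a worsening on propranolol. An acute calming effect on the M1 ratings, or less certainly on S-DAI, would shrink the measured benefit in the same way. The optional baseline covariate would then be a post-randomisation variable. Table 1 holds no other baseline to fall back on.

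**Working it through.** **1. Can the order be settled from the text?**

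| Source | Points to |
|---|---|
| First dental extraction procedure: 30-minute session after ingestion, cross-referenced to the outcome measures | baseline after dosing |
| Table 1: nothing at t = 0, first values at t = 1 | after dosing, if that session is the t = 1 interview |
| Table 2: phobia diagnosis at t = 0, though made in the interview before randomisation | t = 0 is the pre-dose session, so t = 1 could be the later one |
| First preoperative assessment and Treatment allocation: interview and questionnaires, then randomisation | baseline before dosing |
| Table 2: M1 ratings at t = 1, though made in the interview before randomisation | t = 1 is the pre-dose session |

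The two Table 2 entries come from the same interview but carry different time labels, so the tables cannot decide the matter. The arrival time can also be read in two ways: 1 hour 15 minutes before the ingestion appointment (pre-dose), or the same interval before surgery, which is the stated time of dosing. No sentence says outright whether S-DAI, M1 vividness/emotional charge or heart rate/blood pressure precedes the capsules.

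**2. The planned sample size.** Inputs from Sample size calculation: f = 0.25, ρ = 0.50, two measurements, α = 0.05, power 0.80, total N = 34.

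λ = f² × N × m / (1 − ρ) = 0.0625 × 34 × 2 / 0.5 = 8.5, with 1 and 32 degrees of freedom. Power is 0.807. N = 32 gives 0.781, so 34 is reproduced.

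In SD units, f = 0.25 for this interaction is a between-arm difference in change of 4 × 0.25 = 1.0 SD. The SD of the change is √(2 × (1 − 0.5)) = 1.0 SD.

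**3. If the S-DAI baseline is post-dose.** Let the drug lower the active-arm baseline by c SD, with follow-up unaffected. The values of c are assumed.

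- Change score: the effect is 1 − c, so λ = 8.5 × (1 − c)².
- Baseline as covariate, with ρ = 0.50 and equal SDs: the effect is 1 − 0.5c and the residual SD is √(1 − 0.25) = 0.866.
- Chance that a two-sided t-test with 17 per arm flags the baseline shift.

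| c | λ | Power, change score | Power, covariate (about) | Shift flagged |
|---|---|---|---|---|
| 0 | 8.5 | 0.807 | 0.90 | 0.05 |
| 0.1 | 6.885 | 0.721 | 0.87 | 0.06 |
| 0.2 | 5.44 | 0.619 | 0.84 | 0.09 |
| 0.3 | 4.165 | 0.508 | 0.79 | 0.14 |

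The covariate column ignores the small variance penalty from the imbalance itself, which takes off at most 0.01.

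**4. If heart rate is post-dose.** Let the acute drop at baseline be a and the lasting benefit at follow-up be b. The difference in change (propranolol minus placebo) is (−b) − (−a) = a − b. Assume b = 5 bpm. With a = 0 the result is −5, the true benefit. With a = 5, 10 and 15 it is 0, +5 and +10 bpm. The sign reverses once a exceeds b. Neither a nor b is given in the documents.

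**The case against.** The strongest reply is that the protocol may well intend a pre-dose baseline. It describes a preoperative assessment with questionnaires, then randomisation, then dosing, and Table 2's M1 ratings fit t = 1 being that assessment. The word screening for the post-dose session also echoes the t = 0 label rather than t = 1. This stands: a reader might infer from the post-dose session and Table 1 that the baselines are contaminated and that t = 1 is established as post-dose, but the documents do not support that as settled fact.

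A reader might also infer that the check for baseline differences would detect a drug effect and adjust it away. The figures do not bear this out. Shifts of 0.1 to 0.3 SD would be flagged with probability 0.06 to 0.14, against 0.05 by chance. Where the covariate was used, it would halve the distortion relative to a change score, not add to it. It would still be a post-randomisation variable.

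It is also fair to say that the sizes are assumed. S-DAI is the protocol's trait measure, and nothing in the document shows a single dose moving it within an hour; the acute evidence cited in the Background concerns state anxiety during injection. A session within the absorption hour need not see the full drug effect.

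None of this removes the contradiction. Nor is it detail that an article leaves to the full protocol: the schedule is stated, and the statements disagree.

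**Conclusion.** The point holds as an inconsistency with a conditional bias. The document does not fix the baseline of the primary outcome and of the memory and physiological secondary outcomes as pre-dose, and one natural reading makes it post-dose.

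If it is post-dose, the consequences differ by measure:

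- **Heart rate and blood pressure.** The change is biased against propranolol. For heart rate, with an assumed lasting benefit of 5 bpm and acute drops of 5 to 15 bpm, the apparent difference runs from 0 to 10 bpm in the wrong direction.
- **M1 vividness and emotional charge.** Some dilution is plausible, of unknown size.
- **S-DAI.** The effect is least certain. Assumed shifts of 0.1 to 0.3 SD reduce change-score power from 0.81 to between 0.72 and 0.51; with the covariate it stays at about 0.87 to 0.79, against 0.90 with no shift.

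If it is pre-dose, none of this applies and only the wording needs repair. The planned N of 34 is arithmetically correct either way. If the values were post-dose, no analysis could recover a true baseline.

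**What to change.** Schedule S-DAI, M1 vividness/emotional charge and heart rate/blood pressure during M1 recall in the interview before randomisation and capsule ingestion. Define those values as baseline in Table 1 and in the sections First dental extraction procedure, Primary outcome measure and Secondary outcome measures. Align the t = 0 and t = 1 labels in Table 2 with the same order. A post-dose recall may remain as a procedure, but no post-dose value should serve as baseline or covariate. If practice is already pre-dose, a clarifying sentence and the table edits are enough.

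The trial is still recruiting. For patients already enrolled, flag records whose baseline was post-dose and, for heart rate and blood pressure, compare the arms at follow-up without that value. At a correlation of 0.50 this costs no precision against a change score, since the variance of the change is 2 × (1 − 0.5) = 1 times that of a single measurement. The protocol assumes that correlation for S-DAI only, so for heart rate and blood pressure it is an assumption.

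The cost is a same-visit reordering, a small amendment and a somewhat longer pre-dose interview. M1 is already elicited there, and N stays 34.

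A separate, minor point: the Primary aim has "two 40 mg propranolol capsules 1 hour prior to dental extraction", whereas First dental extraction procedure gives 1 hour 15 minutes. These passages must be reconciled.

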#### First postoperative assessment

At completion of the surgical procedure, the dental surgeon will fill out the CRF containing the operative variables. Before leaving the clinic, the patient will again be shortly interviewed by the investigator. Only after the first dental extraction procedure will another semi-structured interview be conducted. This is meant to construct an approximately 30-second personal memory script portraying this first dental extraction procedure that the participant has just experienced (M2). The participant will subsequently receive one final capsule containing 40 mg of propranolol or placebo. The participant will be asked to fill in a small “intrusions diary” at home.

#### Second dental extraction procedure

At the 1-month follow-up, a second dental extraction at the hospital will be performed, this time without the study medication. Administration of all questionnaires before and after the procedure will be repeated, but this time, no full-intrusions interview will be conducted. During the second procedure, a regularly used local anesthetic solution of articaine 4 % with adrenaline (1:200,000) will be administered. At completion, the surgeon will fill out another CRF, and the participant will be asked to keep another “intrusions diary”.

#### Methods to maximize participant adherence to the intervention and follow-up procedures

The day before the first and second treatment, participating patients will receive a text message on their cell phone and an email at their home address reminding them of the appointments. The day after the first and second treatment, participants will receive another text message or email reminding them to fill out the “intrusions diary”.

### Investigational products

#### Active substance

The active medicinal product investigated is Propranolol HCl (a lipophilic ß_1,2_-adrenoreceptor antagonist) 3 x 40 mg tablets overencapsulated in three blue-white, size 00, oral capsules, complemented with microcrystalline cellulose PH 102.

The preoperative dose of 80 mg propranolol is intended to mitigate perioperative state anxiety. Previous research has shown that a dose of 40 mg of oral propranolol was inadequate to reduce the acute hyperadrenergic anxiety states in recently psychologically traumatized individuals [58], and that administration of 80 to 120 mg of oral propranolol significantly reduced self-reported anxiety during injection of local intraoral anesthesia in patients with dental phobia [41].

The administration of 40 mg of propranolol immediately postoperatively is targeted at blocking the reconsolidation process of emotional memory. Research suggests that a “window of opportunity” for ß-adrenergic modulation of memory reconsolidation exists for some hours after retrieval of a fear-related memory [50, 59]. Because propranolol has a half-life of approximately 4 hours, the initial preoperative dose may not exert sufficient ß-adrenergic receptor antagonizing effects during the full reconsolidation period.

#### Placebo comparator

The placebo comparators are three capsules, visually identical to the active substance, filled with pharmacologically inactive microcrystalline cellulose PH 102 as a sole ingredient.

### Sequence generation, allocation concealment and implementation

The random allocation sequence will be computer-generated. The allocation list is available only to the GMP-certified Hospital Pharmacy, where the study medication was produced and labeled, and to the Hospital Pharmacies of both study locations, where the study medication is conserved and provided. The manufacturer of the investigational medicinal products (GMP-certified Hospital Pharmacy) will randomize the allocation sequence; bottles consecutively issued by the study pharmacies will therefore contain either propranolol or placebo capsules in a random order.

### Blinding

Trial participants, investigators, data collectors, the statistician, and outcome assessors are blinded to the study-group assignments. Only the producing and providing hospital pharmacy staff are not blinded; the allocation of a participant will be unmasked before the end of the trial only in case of a serious adverse event related to the study medication.

### Study outcome measures

Dependent variables were derived from the questionnaires listed below (see Tables 1 and 2).

**Table 1 Tab1:** Primary and secondary study outcome measures

		Measures			
		Primary outcome	Secondary outcomes		
		Trait anxiety (S-DAI)	State anxiety (VAS score)	Vividness/emotional charge (M1) propensity (VAS scores)	Physiological response (HR/BP)
Screening (t = 0)	Screening interview				
Intervention (t = 1)	Preoperative interview	X		X	X
	Postoperative interview		X		
Follow-up (t = 2)	Preoperative interview	X		X	X
	Postoperative interview		X		

*Note:*
*BP* blood pressure, *HR* heart rate, *M1* crucial fear-related memory, *S-DAI* Short version of the Dental Anxiety Inventory, *VAS* visual analog scale

**Table 2 Tab2:** Tertiary outcome measures

		Measures							
		Operative variables/qualitative aspect of the surgical experience (VASs)	Test of blind	IES	FCDS	Qualitative aspect of memory M2 (VASs)	Qualitative aspect of memory M1 (VASs)	Intrusions diary	Specific phobia diagnosis
Screening (t = 0)	Screening interview				X				X
Intervention (t = 1)	Preoperative interview			X			X		
	Postoperative interview	X	X			X		X	
Follow-up (t = 2)	Preoperative interview			X	X	X	X		X
	Postoperative interview	X						X	

*Notes:*
*FCDS* fear of stimuli compromising the dental setting, *IES* Impact of Event Scale - Revised, *M1* crucial fear-related memory, *M2* memory of recent dental extraction procedure, *VAS* visual analog scale

#### Primary outcome measure

The primary aim is to assess the reduction in the dental trait anxiety score in the propranolol versus the placebo control group (Table 1). The change from baseline to 1-month follow-up in dental trait anxiety will be indexed with the Dutch version of the *Short version of the Dental Anxiety Inventory* (S-DAI) [60]. The items (for example, “when I know the dentist/oral-maxillofacial surgeon is going to extract a tooth, I am already afraid in the waiting room”) are answered on a five-point Likert-type scale, ranging from “totally not applicable to me” (1) to “totally applicable to me” (5). Total scores on this questionnaire range from 9 to 45. The clinical cut-off score for a patient to apply for treatment in a specialized dental fear clinic is a minimum of 28 points on the S-DAI [61].

#### Secondary outcome measures

The self-reported state anxiety during dental treatment from baseline to 1-month follow-up will be indexed using a visual analog scale (Table 1). Patients are asked to rate the question “How much anxiety did you experience during the last treatment” using a standardized continuous self-report VAS ranging from “no anxiety at all” 0 to “extreme anxiety” 100.

Change from baseline to 1-month follow-up in self-reported vividness and emotional charge of the crucial fear-related memory will be measured using visual analog scales that assess key characteristics of the traumatic memory that initiated or exacerbated the dental anxiety (M1) (Table 1). Patients will be asked to rate the questions “how vivid or detailed is the memory, if you bring up the memory now” and “how much emotion does the memory evoke, if you bring up the memory now” using a continuous self-report VAS ranging from “no (anxiety/emotion) at all” (0) to “extremely much (anxiety/emotion)” (100).

Change from baseline to 1-month follow-up in physiological parameters during recall of the crucial fear-related memory (M1), will be assessed by bringing up the memory (M1) while the psychophysiological response (heart frequency per minute and blood pressure in mm Hg) will be indexed using an upper arm blood pressure measuring device (CE: 0297) (Table 1).

